### Randomisation

The randomisation to the intensive STRONG Program or standard care takes place via the Redcap program as recommended in the Capital Region with stratification for each centre as well as for one, two or three-to-five co-existing risky SNAP factors and computer-generated blocks ranging from 2 to 5. The randomisation system is accessible around the clock via computer.

### The control group

The control group receives the standard care regarding the SNAP factors. This includes the participant information, weight loss and smoking cessation initiatives, according to local routines, and access to support offered outside the project.

The project does not involve placebo intervention in the control group.

### *The practical procedures, studies, and outcomes*

The 400 patients are recruited at the involved surgical departments:

- Herlev Hospital ([name]),
- Regionshospitalet Horsens ([name]),
- Sjællands Universitetshospital Køge ([name]),
- Sjællands Regionshospital Holbæk ([name]).
- - more departments – also in the private sector – may be included if necessary and after extended approval from the Ethical Scientific Committee and the Danish Data Protection Agency.

Standard protocol for SNAP at Horsens: Weight loss information and smoking cessation as BMI < 30 and smoking cessation (without verification by urine cotinine test) are mandatory.

Standard protocol for SNAP at Zealand University Hospital, Køge: Weight loss information, smoking cessation - active surveillance, and follow-up by nurses aiming at BMI < 35 and smoking cessation (without verification by urine cotinine test) mandatory.

Standard protocol Herlev University Hospital: The aim is a general optimization prior to surgery, including regarding BMI and smoking (without verification by urine cotinine test).

Standard protocol Zealand Regional Hospital, Holbæk: The aim is a BMI under 35 and optimization of any comorbidity prior to surgery. For operation of major hernia of 10 cm or more, it is recommended to stop smoking six weeks preoperatively (without verification by urine cotinine test).

After informed consent, patients are included and allocated to either the 6-week STRONG intervention or the control group. Data collection takes place at baseline, after 6 weeks/at time of surgery, and postoperatively after 1, 3 and 6 months at the local surgical department. The data are included in the databank in Redcap, and blood and urine samples are transferred to the established project biobank at the Parker Institute. For the long-term follow-up on health, further data are drawn from national health registries up to 2-years after the inclusion (project flow in figure 1).

### The studies

The project is constituted by several sub-studies all based on data from the RCT with 400 patients as specified in Chapter 2.

### Outcomes and data collection (Table 1)

Postoperative complications (within 1, 3, 6 months after surgery): The primary outcome is the number of patients with > 1 complication, defined by requiring documented treatment, categorized in accordance with the Clavien-Dindo grading and the Comprehensive Complication Index (CCI). They include adverse events and side effects. Secondly, length of stay, second surgery, revisits and – admissions at hospital, visits in primary care, time back to work or previous activities.

Successful risk reduction at follow-up/at surgery: Defined as SNAP below risk level validated as described in chapter 2; for obesity BMI < 30 or at least 5% and max 10% loss of body fat mass preoperatively (0.5–1 kg/weekly without developing malnutrition). Data are collected via logbook and validation.

For frailty: In addition to pI-protein, the frailty level (0-5, 0 is best) is measured by Fried's Modified Frailty Score according to Blammers as that is associated with development of complications. It includes five criteria:

- Slowness: Performance time in the walking test,
- Weakness: Hand grip strength measured by a dynamometer,
- Exhaustion: Responding "All the time" or "Often" to the item "I feel everything is an effort / I can't get going" in the Hospital Anxiety & Depression Scale.
- Weight loss: Self-reported 5 kg over the last year
- Low activity: Below 3 MET

Health (at baseline, after 6 weeks/at surgery, and 6 months postoperatively): This is measured by the health-related quality of life measured by EQ-5D with 5 dimensions and the overall health measured with a scale from 0 to 100 with a higher score representing a better health. Within 2 years of follow-up, the morbidity is measured as visits and stay at hospital as well as visits in primary care and prescribed medicine and grouped diagnoses groups as well as mortality.

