### Brief Summary (English)

This national project is the first to include all SNAP factors (Smoking, Nutrition - both obesity & malnutrition - Alcohol, and Physical activity) in a combined intervention aiming at risk reduction for patients scheduled for ventral hernia repair. It will generate new knowledge of the effect on risk reduction via intensive lifestyle intervention 4 weeks prior to surgery.

The overall goal is to reduce the inequity in health via perioperative STRONG lifestyle intervention aiming at a better health gain by surgical risk reduction at short time and improved health on longer time. In total, 2x200 surgical patients disadvantaged by preoperative risky lifestyle will participate.

The primary outcome is postoperative complications. Other important outcomes are clinically relevant lifestyle improvements, frailty and comorbidity symptoms, patient motivation and reflections, health-related quality of life and cost-effectiveness on short and longer time. In addition, possible dose responses between lifestyle at surgery and complications, health & costs, and association between self-reported and validated lifestyles.

This project builds further on the ongoing and smaller STRONG-Cancer project for risk reduction at surgery with change in lifestyle as the primary outcome, approved in 2020 (H-20081571; P-2020-95).

Collaboration among:

4 Surgical Departments at:

HERLEV Hospital ([name]), HORSSENS

Regional Hospital ([name]), Zealand

University Hospital KØGE

([name]), and

Holbæk Hospital ([name])

and

The Danish Centre for Health

Economics at University of

Southern Denmark ([name])

and

The STRONG Team at WHO-

CC, Parker Institute at

Bispebjerg-FREDERIKSBERG

Hospital ([name])

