### The hypotheses

The primary hypothesis is that STRONG halves the postoperative complications within 1 month compared to the daily routines.

Secondly, improvement of postoperative complications after 3 and 6 months, risky SNAP lifestyles, health, and the cost-effectiveness as well as improvement of health and costs after 2 years.

In addition, we hypothesise associations

- between preoperative patient reflections and successful change of SNAP factors
- as a dose-response of SNAP factor improvement and complications, as well as predictors for complication-free hernia repair
- as a dose-response of SNAP factor improvement and health gain, as well as predictors for a health gain
- between self-reported and validated SNAP factors.

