### The outcomes

The primary outcome is postoperative complications according to the Clavien-Dindo classification. Secondary outcomes are improvement of risky SNAP lifestyles (self-reported and validated), risk evaluation (according to the lifestyle categories in the ASA-score), patient reflections, health (measured by health-related quality of life, symptoms of frailty, and co-morbidity) and costs (measured as individual direct and indirect healthcare costs per patient based on perioperative costs, time back to work or reuptake of previous activities, total stay, and visits/contact to hospital and primary healthcare (from the national health registries).

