| Smoking (n° cigarettes/day, Nutrition (intake), Alcohol (n° drinks/week), Physical activity (min/day) | X         | X                      | X                    | X                       |
| EQ-5D (HRQoL)                                                                                         | X         | X                      | X                    | X                       |
| Adverse events                                                                                        |           | X                      | X                    | X                       |
| Status (validated)                                                                             |           |                        |                      |                         |
| Blood + urine: Alcohol & Nicotine biomarkers, Hgb, Albumin, Protein, ASAT, Bilirubin                  | X         | X                      | X                    | X                       |
| Weight and bio-impedance, height,                                                                     | X         | X                      | X                    | X                       |
| Frailty score (weight loss, handgrip, walking test, exhaustion, level of activity)    | X         | X                      | X                    | X                       |
| ASA-score                                                                                             | X         | X                      | X                    | X                       |
| Postoperative complications                                                                    |           |                        |                      |                         |
| Complications /yes/no)                                                                                |           |                        | X                    | X                       |
| Clavien-Dindo grade and CCI                                                                           |           |                        | X                    | X                       |
| Stay in hospital                                                                                      |           |                        | X                    | X                       |
| Second surgery                                                                                        |           |                        | X                    | X                       |

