### 4. Statistical considerations: Power calculation

The power calculation is based on the literature as presented above, thus aiming at halving of postoperative complications after intensive programs for smoking, alcohol, and malnutrition. The impact of physical activity is lower, and obesity is sparsely investigated but targeting co-existing SNAP like STRONG should increase the effect due to interactions. Therefore, the main hypothesis is clinically relevant. For ventral hernia in high-risk patients, STRONG would expectantly half the overall complication rate from conservatively 20% to 10%. When using 80% power and 2 x alpha=0.05 we get 2 x 199 participants. This also covers the secondary outcomes regarding lifestyle improvements and costs.

In case of dropping out, the patients are asked to allow follow-up via the medical record system and a telephone interview. It is our experience from previous studies that 90% the drop-out patients accept this. Therefore, the development of complications as the primary outcome will be available for close to all randomised patients. We use block randomisation in rather small groups, which would only to a minimal degree impact the distribution between the intervention and control groups.

In study 4 the prevalence of risky SNAP factors on all patients that potentially could be screened for eligibility in study 1 (about 2 x the included numbers = 800 patients) will be reported as frequencies and 95% CI and analyzed for the potential maximum risk reduction and effects, if they would have received a related STRONG intervention. If possible, the potential will be analyzed for the most frequent combined risk factors.

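### The primary outcome is written as more than one complication per patient, but the hypothesis, the data form and the sample size all concern any complication

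*Protocol*

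**What the plan says.** The operational definition is in the Protocol, Outcomes and data collection (Table 1): "The primary outcome is the number of patients with > 1 complication, defined by requiring documented treatment". No other section defines who counts as an event.

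The other relevant places read differently:

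- Section 2a, The outcomes, sets no count: "The primary outcome is postoperative complications according to the Clavien-Dindo classification".
- Section 2a, The hypotheses, sets no threshold of two and fixes the time: "The primary hypothesis is that STRONG halves the postoperative complications within 1 month compared to the daily routines". It also plans to look for predictors of a repair without complications, which is a contrast of none against at least one.
- Table 1 has a binary item, "Complications /yes/no", collected at 30 days and again at 3 and 6 months.
- Section 4 sizes the trial on the overall rate: "STRONG would expectantly half the overall complication rate from conservatively 20% to 10" per cent, and then "When using 80% power and 2 x alpha=0.05 we get 2 x 199 participants". The Brief Summary plans 2 x 200.
- The section on ventral hernia repair and SNAP factors describes one of the trials cited for that rate, a smoking cessation trial, as reporting any complication in its hernia subgroup (6/21 against 10/17).

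The protocol nowhere gives a rate for two or more complications or a reason for such a threshold.

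**The concern.** More than one complication means at least two. A patient with a single treated wound infection would then count as event-free, on the same footing as a patient with no complication. The protocol notes that complications in the cited hernia subgroup were mainly wound complications, so single events could well be common.

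Patients with two or more complications are a subset of those with any. The control rate for the literal endpoint therefore cannot exceed the rate for any complication that the plan assumes, and it is lower as soon as some complicated patients have only one event. With the same relative effect and the same number of patients, power falls. An analyst who follows the definition to the letter would run the primary test on an endpoint with no stated event rate and no power calculation behind it.

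**Working it through.** **Inputs from the Protocol.** Control rate 0.20 and STRONG rate 0.10; two-sided alpha 0.05; power 80%; stated size 199 per arm (section 4). Planned 200 per arm (Brief Summary). Fisher's exact test for frequencies (section 3a, Analyses).

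**Step 1: reproduce the plan's figure.** For two proportions with pooled variance under the null and no continuity correction,

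n = [1.960 × √(2 × p̄ × (1 − p̄)) + 0.8416 × √(p₁(1 − p₁) + p₂(1 − p₂))]² / (p₁ − p₂)², with p̄ = 0.15.

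- First term: 1.960 × √0.255 = 0.990.
- Second term: 0.8416 × √(0.16 + 0.09) = 0.421.
- n = (1.4106)² / 0.01 = 199.0, so 199 per arm.

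This matches exactly. The sample size therefore belongs to the rate of any complication. At 200 per arm, power for 20% against 10% is 80.2% by the normal approximation and 76.8% by exact enumeration of Fisher's test. The second figure is the fair baseline for the Fisher results below.

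**Step 2: the literal endpoint.** The rate of two or more complications is not in the protocol. Assume that a share s of complicated patients has two or more, in both arms. Then p₁ = 0.20 × s, p₂ = 0.10 × s, and the halving is preserved. At 200 per arm:

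| Share s (assumed) | Rates | Expected patients with event | Power, normal approx. | Power, exact Fisher | n per arm for 80% (normal approx.) |
|---|---|---|---|---|---|
| 10% | 2% v 1% | 4 v 2 | 13% | 4% | 2319 |
| 20% | 4% v 2% | 8 v 4 | 22% | 13% | 1141 |
| 30% | 6% v 3% | 12 v 6 | 30% | 23% | 749 |
| 50% | 10% v 5% | 20 v 10 | 48% | 41% | 435 |
| 75% | 15% v 7.5% | 30 v 15 | 66% | 61% | 278 |
| 100% (same as any) | 20% v 10% | 40 v 20 | 80% | 77% | 199 |

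**Step 3: a different assumption.** Suppose the number of complications per patient is Poisson, matched to 20% and 10% with any event.

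- Control: λ = −ln 0.8 = 0.223; P(≥ 2) = 1 − 0.8 × 1.223 = 2.15%.
- STRONG: λ = −ln 0.9 = 0.105; P(≥ 2) = 1 − 0.9 × 1.105 = 0.52%.

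Exact Fisher power at 200 per arm is 12%. This model implies roughly a fourfold reduction (2.15 / 0.52 = 4.2) rather than a halving, so it is a side check and not the main case.

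**The case against.** The strongest reply is that nobody intends a threshold of two. The sample size, the yes/no item, the hypothesis and the cited any-complication result all point to at least one. An underlined sign meaning at least one can lose its underline when a PDF is read by a program, and the text at hand cannot show whether that happened here. All of this stands. It makes a wording or symbol error the likeliest explanation, and it means that the sample size itself is not at fault.

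It does not remove the point. As read, the one sentence that says who counts as an event contradicts the rest of the document. If the sign turns out to be at least one in the source file, the count is settled without further work.

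A reader might go further in three ways that the documents do not support:

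- **That the trial is underpowered.** This follows only if the literal definition is applied, and its extent depends on a share that the protocol does not give.
- **That the primary time point is undefined**, because the paragraph is headed with 1, 3 and 6 months. The primary hypothesis fixes 1 month and places 3 and 6 months second, and the list of sub-studies separates them as 1A and 1B.
- **That side effects of the programme's own medicines bias the primary comparison against STRONG**, because the paragraph adds "They include adverse events and side effects". That paragraph is headed as complications after surgery, whereas the programme runs before surgery. Table 1 lists adverse events in a separate row that includes the visit at surgery, while its complications block starts at 30 days. Controls may also use support outside the project. Such a bias is not shown.

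**Conclusion.** The primary outcome definition is wrong as written and must be reconciled with the hypothesis, Table 1 and section 4. The contradiction rests on the text alone and needs no assumption. For any complication the plan is sound: 199 per arm is right, and 200 per arm gives 80% power by the approximation used and about 77% with Fisher's test.

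The consequence of following the definition literally is conditional. If the halving is kept, exact Fisher power is about 4%, 41% or 61% when 10%, 50% or 75% of complicated patients have two or more events. The direction of the loss is certain under a constant halving; its size is not. Whether the sign is deliberate, a slip or a conversion loss cannot be settled from this text.

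**What to change.** Check the sign in the source file, then reword the definition in Outcomes and data collection along these lines: *the number of patients with at least one (≥ 1) postoperative complication requiring documented treatment within 30 days after surgery*. In the same sentence, label the 3- and 6-month counts as secondary, as section 2a already does.

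The cost is one sentence. Table 1 already has the yes/no item at 30 days, so no new data and no extra patients are needed, and the power calculation can stay as it is.

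If two or more complications is truly intended, the sponsor should say why, give the expected rates in both arms with their source, and restate the sample size and power for that endpoint.

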### 3c. Interventions

Intervention group: Patients in the intervention group receive minimum five educational sessions over 6 weeks (i.e., about weekly) as an integrated prehabilitation program tailored to meet the

individual patient's need for risk reduction at surgery, see Table 2 and 3. It is introduced via the surgical 'Engage in the process of change'. The smoking intervention follows the Gold Standard Programme GSP, which has been translated to the standardized alcohol cessation intervention, exercise training programme, and nutritional intervention.

Project nurses from the participating centre, who have taken part in a 5-day educational program followed by practical training in the Gold Standard Programme (GSP), provide the intervention. The project leader ([name]) of the trial ensures that counsellor follows the principles of the GSP program by regular discussion of the intervention.

Table 2. Weekly sessions after inclusion (Preop: preoperatively)

|                                  | Week 1 | Week 2 | Week 3 | Week 4 | Week 5 | Week 6 Follow-up
+ continued preop. |
|----------------------------------|--------|--------|--------|--------|--------|----------------------------------------|
| Smoking cessation                | X      | X      | X      | X      | X      | X                                      |
| Nutrition program (malnutrition) | X      | X      | X      | X      | X      | X                                      |
| Nutrition program (obesity)      | X      | X      | X      | X      | X      | X                                      |
| Alcohol cessation                | X      | X      | X      | X      | X      | X                                      |
| Physical Activity                | X      | X      | X      | X      | X      | X                                      |

Table 3. The patient education program in the Gold Standard Programme (GSP)

| Week number                | Education subject                                              |
|----------------------------|----------------------------------------------------------------|
| 1 (at inclusion)           | Level of motivation, ambivalence, pros and cons (see Appendix) |
| 2                          | Dependence, withdrawal symptoms (experience and expectations)  |
| 3                          | Relapse (description and management)                           |

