## STRONG – Hernia, Version 5 (12-05-2024)

All participants are included after informed consent and can withdraw their consent without further explanation and without influence on the treatment and care in the department. Patients, who withdraw the informed consent or say no thank you to participate in the randomised trial are asked about a separate informed consent for being followed-up via the medical records and the health registries.

The informed consent is collected timely to allow for 4-6 weeks prehabilitation with the STRONG program. If the operation is postponed, the prehabilitation period is extended until surgery (e.g., 8-

|                                              | 2023 | 2024 | 2025 | 2026 |
|----------------------------------------------|------|------|------|------|
| Protocol article writing                     | X    |      |      |      |
| Study 1-A Inclusion & data collection | X    | X    | X    |      |
| Analysing +Article writing                   | X    | X    |      |      |
| Study 1-B Data collection             | X    | X    | X    | X    |
| Analysing + Article writing                  |      | X    | X    | X    |
| Study 2 Data collection               |      | X    | X    | X    |
| Analysing + Article writing                  |      |      | X    | X    |
| Study 3 Data collection               |      | X    | X    | X    |
| Analysing + Article writing                  |      |      |      | X    |
| Study 4-A Analysing + Article writing |      |      | X    |      |
| Study 4-B Analysing + Article writing |      |      |      | X    |
| Study 4-C Analysing + Article writing |      | X    |      |      |
| Study 4-D Analysing + Article writing |      | X    |      |      |
| Running information of the project           | X    | X    | X    | X    |

12 weeks). They are also welcomed to use the project hotline in case of further questions and considerations. Participants are included only after informed consent and would then be randomized to either the intervention or control group.

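### The frailty score counts intended weight loss as frailty, and the obesity success ceiling can clash with the programme's own pace of weight loss

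*Protocol*

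**What the plan says.** Chapter 3, Outcomes and data collection, states that "the frailty level (0-5, 0 is best) is measured by Fried's Modified Frailty Score". Its five criteria are walking time, grip strength, exhaustion, low activity and "Weight loss: Self-reported 5 kg over the last year". The weight item gives an amount and a look-back period but does not ask whether the loss was intended.

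Table 1 lists "Frailty score (weight loss, handgrip, walking test, exhaustion, level of activity") at inclusion, at week 6 or surgery, at 30 days and at 3 and 6 months. Section 2a, The outcomes, makes it part of a secondary outcome: "health (measured by health-related quality of life, symptoms of frailty, and co-morbidity").

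The same outcomes section defines successful risk reduction "for obesity BMI < 30 or at least 5% and max 10% loss of body fat mass preoperatively", followed by the pace "0.5–1 kg/weekly without developing malnutrition".

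On duration, section 3c says "Patients in the intervention group receive minimum five educational sessions over 6 weeks". Section 12 plans for 4–6 weeks of prehabilitation and adds "If the operation is postponed, the prehabilitation period is extended until surgery", with 8–12 weeks as the example.

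**The concern.** One event, planned weight loss in an obese participant, can be a success on the obesity outcome and a deterioration on the frailty outcome. Randomisation does not remove this, because the allocated programme itself causes the item to be scored. In sub-study 5B, which relates SNAP improvement to later health, obesity improvement and a worse frailty score become linked by definition wherever frailty serves as the health measure.

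The second issue is within the success rule. A pace and a 10% maximum stand in one sentence, but no fat mass is given and the programme's length varies. A participant who keeps to the pace may pass the maximum. If BMI is then still 30 or more, the wording does not count that participant as a success.

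**Working it through.** **Plan's own figure.** The protocol gives no calculation for either outcome. Its one calculated figure, 2 x 199 for complications of 20% versus 10% (80% power, two-sided 0.05), is reproduced as 199 per arm without continuity correction. It does not depend on this point.

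**Step 1: weight loss implied by the pace.** Loss = rate x weeks, with rate 0.5–1 kg per week. The rate needed for 5 kg is 5 / weeks. The item is read as 5 kg or more.

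| Weeks | Loss (kg) | Rate needed for 5 kg (kg/week) | Within the stated pace? |
|---|---|---|---|
| 4 | 2–4 | 1.25 | No, never reached |
| 6 | 3–6 | 0.83 | Upper part only |
| 8 | 4–8 | 0.63 | Most of the range |
| 12 | 6–12 | 0.42 | Every stated rate |

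**Step 2: does the loss stay in the look-back window?** Twelve weeks of programme plus about 26 weeks to the 6-month visit is 38 weeks, which is under 52. Loss from the first week still counts at the last frailty visit.

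**Step 3: possible size among obese participants.** The protocol gives no distribution of weight loss, so these inputs are assumed: normal, SD 2.5 kg, mean loss 3–6 kg on STRONG and 0–3 kg in control. The shift in mean frailty score from this item is P(loss ≥ 5 kg on STRONG) − P(loss ≥ 5 kg in control). For 4.5 versus 1.5 kg:

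- STRONG: 1 − Φ((5 − 4.5)/2.5) = 1 − Φ(0.2) = 0.42
- Control: 1 − Φ((5 − 1.5)/2.5) = 1 − Φ(1.4) = 0.08
- Shift: +0.34 points

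| Mean loss on STRONG | Control 0 kg | Control 1.5 kg | Control 3 kg |
|---|---|---|---|
| 3 kg | 0.19 | 0.13 | 0.00 |
| 4.5 kg | 0.40 | 0.34 | 0.21 |
| 6 kg | 0.63 | 0.57 | 0.44 |

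If 40% of participants are obese (assumed), 0.34 becomes 0.40 x 0.34 = 0.14 over the whole arm. Participants who already score the item at baseline would reduce it further.

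**Step 4: pace against the 10% maximum.** Fat mass is not given. For an assumed 30–60 kg, 10% is 3–6 kg. At 40 kg:

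- 4 weeks: 2/40 to 4/40 = 5–10% if all loss is fat, exactly the stated window
- 6 weeks: 3/40 to 6/40 = 7.5–15%; if 75% of the loss is fat, 2.25/40 to 4.5/40 = 5.6–11.25%
- 12 weeks: 6/40 to 12/40 = 15–30%; if 75% is fat, 11.25–22.5%

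**Step 5: how far BMI < 30 rescues such patients.** At an assumed height of 1.70 m, 6 kg is 6/2.89 = 2.1 BMI units and 12 kg is 4.2. Patients entering above about BMI 32 (6 weeks) or 34 (12 weeks) would not reach BMI 30 at the stated pace.

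**Step 6: effect of the cap on the contrast.** Using the Step 3 distribution, fat mass 40 kg and 80% of loss as fat (all assumed), the 5–10% window is 2.5–5.0 kg of body weight. Ignoring the BMI route, success at mean losses of 4.5 versus 1.5 kg is 37% versus 26% with the cap and 79% versus 34% without it. At 6 versus 3 kg it is 26% versus 37% with the cap.

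**The case against.** Several counter-arguments have force.

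- **Duration.** Section 5 asks only for screening at least 4 weeks before surgery, and section 12 allows 4–6 weeks. At 4 weeks the stated pace never reaches 5 kg and fits the 5–10% window at 40 kg of fat. This stands: the effect needs the faster pace at 6 weeks, or a longer programme.
- **Control-arm loss.** The centres' standard protocols in chapter 3 also pursue BMI: below 30 and mandatory at one, below 35 at two, general optimisation at the fourth. This stands and shrinks the difference.
- **Other frailty items.** STRONG includes daily exercise, which may improve walking, grip and activity. A reader might infer that a successful STRONG arm will look frailer overall. The documents do not support that, because the net direction of the five-item score is unknown.
- **Instrument labels.** The slowness and weakness criteria carry no cut-offs, so the list may abbreviate a cited instrument whose scoring, like the Danish forms, cannot be seen. This is partly right. However, the weight criterion does state its amount and period and leaves intent out.
- **Dose-response.** Frailty is not a SNAP factor, so it may seem outside those analyses. This fails for sub-study 5B, whose outcome is health, since section 2a counts frailty as health. The later outcomes section lists frailty under its own heading, so the link applies only where 5B uses that component.
- **The 10% limit.** It is written as a maximum, beside a warning about malnutrition. Loss beyond it is therefore not plainly what the programme is meant to produce, and a pace and a maximum can coexist.

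**Conclusion.** The frailty point holds in a limited form. As written, the weight item scores intended loss, is re-scored after the intervention, and can be triggered by the programme's own pace. It works against STRONG by at most one point of five per affected participant. Among obese participants the illustrative shift in the mean runs from 0.00 to 0.63, resting wholly on assumed losses and spread, and it is diluted by non-obese participants. The true size is unknown.

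The ceiling point holds as a need for reconciliation. Over 6–12 weeks the pace can exceed 10% for patients still at BMI 30 or more, depending on a fat mass the protocol does not give.

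A reader might infer that any fat loss above 10% is a failure, or that both outcomes are biased against STRONG. Neither follows. BMI below 30 is an alternative route to success. The cap shrinks the contrast in one illustration and reverses it in another. Both points concern secondary outcomes only; the primary complication outcome is unaffected.

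**What to change.** 1. **Frailty.** For the between-arm and dose-response analyses, use the four-item score (0–4) without weight loss, and report the five-item score alongside. Where intent is recorded, scoring the item only for unintentional loss is an alternative. The four-item score needs no new data. Its cost is a departure from the cited five-item instrument. Intent cannot be recovered from measured weights, so adding the word unintentional to the form helps only at visits still to come.
2. **Obesity success.** The sponsor and clinicians should reconcile the weekly pace, the 10% maximum and the 4–12 week range of programme lengths. The protocol should then state how loss above 10% with BMI still 30 or more is classified in the analysis, and such losses should be tabulated separately by arm. Which clinical limit applies is theirs to decide. The cost is wording and one table from weight and bio-impedance data already planned in Table 1.

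Neither change affects the sample size or the primary analysis.
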